### 3 Version history

The first unblinded analysis of the TARGIT Trial took place in 2010 using a reference date of 02/05/2010, on the recommendation of the DMC. The emphasis was on efficacy and early safety. The results have been published (Lancet 2010; 376: 91-102).

The second unblinded analysis took place in 2012 using a reference date of 01/06/2012, on the recommendation of the DMC in 2010 (two years after the first analysis). The emphasis was on efficacy, and mortality. The results have been published (Lancet 2014; 383: 603–13).

This SAP is for a third unblinded analysis due to take place in 2019 using a reference date of 02/05/2018 on the recommendation of the TSC (completeness of follow-up at least 95% at 5 years and 90% at 10 years). The emphasis will be on all primary and secondary endpoints and subgroup analyses.

## **5 Study title**

TARGIT Trial: An international randomised controlled trial to compare targeted intra-operative radiotherapy with conventional post-operative radiotherapy after conservative breast surgery for women with early stage breast cancer

## **6 Study population**

The study population has been described previously. There are two main strata in the trial. The prepathology stratum includes all patients who were randomised before their cancer was excised. The postpathology stratum includes all patients in whom the tumour had already been excised before randomisation so that for those randomised to TARGIT, re-opening of the wound was required to give targeted intraoperative radiotherapy. As the treatment delivery is so different between these two strata, and as they had separate randomisation tables, these were in fact two trials in parallel and therefore, all results will be presented separately for each stratum.

## **7 Objectives**

### **7.1 Main Objective**

To compare within each stratum, a single fraction of radiotherapy given intra-operatively and targeted to the tissues at the highest risk of local recurrence within a risk-adapted approach with standard post-operative radiotherapy after breast conserving surgery in women with early stage breast cancer in terms of survival without local recurrence in the conserved breast.

### **7.2 Secondary Objectives**

To compare the treatment arms in each stratum with respect to:

- Overall survival (Breast Cancer and Non-Breast-Cancer Survival)
- Disease free survival
- Invasive-disease free survival
- Mastectomy and re-excision rate
- Treatment of local recurrence
- Site of relapse within the breast
- Local toxicity/morbidity

All outcomes in the following subgroups

- Effect of ER and PgR status on the outcomes
- Screen-detected vs symptomatic
- Effect of use of hormone therapy.
- Effect of Grade, node positivity, HER2 receptor status, etc.
- Effect of Centre and/ or Country on the outcomes
- Effect of all other predictive factors on the outcomes
- Re-do the relevant previously performed analyses with updated follow up information
- Outcomes as per treatment received along with subgroup analyses to refine understanding of what happens in the real world.

Additional analysis including Health economic analysis and cosmetic outcome, patient preference may also be undertaken.

## 8 Statistical analysis plan

### 8.1 Preamble

The statistical analysis plan for the analysis performed in 2012-13 stated that the major endpoint would be non-inferiority of local control with a non-inferiority margin of 2.5% at 5 years, for the whole trial and the Prepathology and Postpathology strata.

We have since learnt that non-inferiority analyses are ill understood and controversial. Although our 2.5% margin has been ratified in patient preference studies, it has been recognised as rather arbitrary; for example, the only other randomised trial (ELIOT) trial {Veronesi, 2013 #3853} of intraoperative radiotherapy for breast cancer used a non-inferiority margin of 7%. Two recent papers published in the Lancet on 6-month vs 12-month duration of adjuvant trastuzumab therapy found almost exactly the same results, but diametrically opposite conclusions and contradictory recommendations for practice simply because they had different non-inferiority margins [correspondence in post].

Furthermore, in the last few years, there was been a wide consensus that using p values for assessment of difference between outcomes can be misleading because of misattribution of a clinical significance to statistical significance of the difference. With increasingly large numbers of patients in clinical trials, you can reach the point where “statistical significance” does not correlate with “clinical significance”.

A substantial change in doctor-patient relationship has occurred in the last few years around the world. Unlike the paternalistic approach in which “clinical significance” was judged by the clinician on behalf of the patient, it is now well accepted that this ultimately needs to be judged by the well-informed patient. This assertion has been determined to be both ethically and legally mandated by the UK Supreme Court’s Montgomery judgement

Finally, effect of radiotherapy on controlling local recurrence compared with no radiotherapy in long term follow up randomised clinical trials plateaus at 5 years and no additional difference arises between 5 and 20 years, both clinician and patient can be confident that the absolute difference in local recurrence is highly unlikely to change after the first 5 years.

In the name of probity and transparency we will conduct the statistical analyses in the ways we’ve published in the past but promote the importance of absolute numbers (not relative risks), and emphasise the actual values for the outcomes in each of the randomised arms, that matter to the patient and facilitate their decision-making process. The patient needs to know her chance of being alive without local recurrence – so local recurrence free survival is the relevant statistic, rather than the estimate of local recurrence calculated after censoring patients at the point of their death - which would give the artificial estimate as if patients live forever.

## 8.2 Methodology

The two arms of the trial will be compared on the basis of 'intention to treat': The methods below have been used in the previous analysis

1. Non-inferiority will be tested using the difference in binomial proportions of local recurrence in the first 5 years and its 90% confidence interval using standard methods.
2. We shall also test for any difference in survival function using the log-rank test and Wilcoxon tests, and Kaplan-Meier curves and proportional hazard regression models will be used to account for time-to event and censoring of the data; however, these shall not be used for testing non-inferiority.
3. We shall also use the integrated difference of the two survival functions to quantify the difference between the Kaplan-Meier curves for local recurrence and local recurrence free survival
4. In order to reduce the assumption of normal distribution in the above models, we shall also use the recently described method of restricted mean survival time approach for analysis of all outcomes

For the primary end point of survival without local recurrence, given the difficulties in understanding the concept of non-inferiority and the criticism that the 2.5% margin may be considered arbitrary, we will describe the main results in terms of the absolute number of events as well as 5-year Kaplan-Meier estimate (and its 95% CI) of local recurrence and local recurrence free survival for each of the randomised arms of the trial.

For the analysis of overall survival, breast cancer survival and non-cancer survival, we shall report the absolute number of events, 5-year KM estimate as well as the analyses to test the null hypothesis of equality.

Statistical significance will be defined as per the current alpha spend. If p values are used, then, for local recurrence statistical significance will be at  $p < 0.001$  (using the Lan-DeMets spending function method) (it was 0.01 at the last analysis), and for survival it will be  $p < 0.025$  (it was 0.05 at the last analysis).

We shall also consider performing these analyses using the Bayesian methods using meaningful priors from previous analyses.

We shall transparently display the results of all analysis.

The baseline comparisons between the two groups will be done using chi-squared test for categorical variables and independent two sample t-test for all continuous variables.

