## 10 Outcomes

### Completeness

- 1.1 A patient is considered to have complete follow up if they **are dead or withdrawn**. “Withdrawn” means the patient has withdrawn consent for further follow-up information to be collected.
- 1.2 A patient is considered as having **recent follow up** if their status is known within 1 year before the reference date for completeness (2 May 2018),
- 1.3 Completeness is assessed at 3 time points
  - 1.3.1 5-years – the usual time to report
  - 1.3.2 10-years – protocol specifies at least 10 year follow up of every patient.

Thus, a patient is considered to have

**5-year complete follow up** if they have at least 5 years of follow up or have a recent follow up or are dead/withdrawn – this was 93.5% at the time of the last publication

**8-year complete follow up** if they have at least 8 years of follow up or have a recent follow up or are dead/withdrawn

**10-year complete follow up** if they have at least 10 years of follow up or have a recent follow up or are dead/withdrawn

Completeness is judged by the following criteria by the TSC

1. Proportion with complete follow up should be high in each stratum
2. Patients’ death is a major cause of not attending the clinic – and hence absence of status of follow up. Therefore, the mortality rate of a centres/countries should be similar to that of the gold standard centres as it would mean that the follow up is complete -

RD = reference date for completion of follow up, nominally 02/05/2018

N5 = number of patients with at least five years of follow-up (from date of randomisation).

N8 = number of patients with at least eight years of follow-up (from date of randomisation).

$N_{10}$  = number of patients with at least ten years of follow-up (from date of randomisation).

$N_1$  = number of patients seen within previous 58 weeks (1 y plus 6 week window) of Reference Date

$N_f$  = include if  $N_{5/8/10}$  or  $N_1$ , the number of patients with adequate follow-up

$D_{all}$  = number of patients randomised (3451)

$D_{cens}$  = number of patients dead or withdrawn before 5 years

The median follow-up will be determined on the population:  $D_{all}$  and  $(D_{all} - D_{cens})$

**Survival without local recurrence** – the number alive without local recurrence (as 1 above) (censored=last date known to be alive or withdrawn)

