A cox- proportional hazard model will be used for analysis of any other predictive factors including variables such as age, tumour size, grade, HER2 status, axillary nodal involvement, vascular invasion, margin, whether screen detected or not. Influence of factors such as ASTRO and/or ESTRO criteria, timing of 1st surgery/biopsy in terms of menstrual cycle, time of the day of delivery of radiotherapy, height, weight, bra size, surgical technique and size of applicator used for TARGIT, dose prescription used for TARGIT, fractionation regime for EBRT, delay between initial surgery and delivery of TARGIT in the postpathology stratum, centre and country, use of systemic therapy, or other factors will also be explored provided sufficient data is available. Significant factors will be reported with absolute differences, and/or hazard ratios and 95%CI.

We shall also perform all the analysis for the first 1222 and 2322 patients recruited in the trial, referred to as the Earliest and Mature cohorts in the 2013/14 Lancet publication. We shall also perform these analyses for the first n number of patients in the pre-pathology stratum to enable a comparison with other trials of partial breast irradiation, where n matches the number of patients in those trials.

We shall describe completeness of follow-up, mastectomy rates, proportion of patients suspected and investigated to have local recurrence in each randomised arm, treatment of local recurrence, number of uncontrolled local recurrence at the time of death and use of EBRT in presence of high risk factors and the effect of radiation fractionation on toxicity. For completion, we shall analyse the cancer, toxicity, overall survival and non-breast-cancer survival outcomes as per treatment received (those that received only TARGIT, both TARGIT and EBRT and EBRT only), however, the results of these artificially created groups need to be interpreted with the consideration that TARGIT treatment is only recommended within a risk-adapted approach.

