### STATISTICAL CONSIDERATIONS

#### 9.1 Patient Numbers and Power Calculations

The objective of the trial is to determine whether the use of intra-operative radiotherapy gives equivalent rates of local control to those obtained using external beam treatment.

This is a Non-Inferiority Trial – One Sided design and we have selected a clinically meaningful non-inferiority margin  $\delta_0 > 0$ . We are interested in testing  $H_0: \delta = \delta_0$  versus  $H_1: \delta < \delta_0$  using a one-sided level- $\alpha$  test with power  $1 - \beta$  to reject  $H_0$  when  $\delta = 0$ .

We have defined the power calculations for this trial using absolute values for local breast relapse. Estimates have been obtained from published data. The CRC Trial compared the outcome of patients with good prognosis early breast cancer who had undergone breast conserving surgery and randomised to post-operative radiotherapy, demonstrated a local recurrence rate of 9% at five years in the arm treated with conventional radiotherapy. The World Overview of radiotherapy in breast cancer showed a baseline rate of about 7.8% at about 10 years. However most of these trials were started in or before 1985 and the techniques of giving radiotherapy have much improved since then such that many papers are reporting much lower rates with conventional radiotherapy.

With a baseline relapse rate of 6 % at 5 years and allowing an absolute increase or decrease in relapse rate of 2.5% (the non-inferiority margin) with 1116 patients randomised to each treatment will give a power of 80% (see Table). Thus if the recurrence rate in the IORT arm is greater than 8.5% (or lower than 3.5%) there will be an 80% chance of demonstrating a difference. If the absolute rate of recurrence is lower e.g. 5% we would have about an 85% chance of detecting a difference. This trial therefore requires a total of 2232 patients to have adequate power to meet the primary objective.

|                      | Relapse rate | Power      |            |             |             |             | Confidence Interval      |       |
|----------------------|--------------|------------|------------|-------------|-------------|-------------|--------------------------|-------|
|                      |              | 60%        | 70%        | 80%         | 90%         | 95%         | Lower                    | Upper |

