### 9.4 Statistical Analysis

The major endpoint is the incidence of local recurrence. This will be compared on the basis of 'intention to treat' (i.e. all randomised patients will be analysed) and the logrank test will be used. This will be performed once the baseline data have been compared to test the randomisation and to define whether any stratified analyses are required. In addition ratios of radiological lesion size to clinical and pathological size, and of specimen weight will be compared to ensure that the extent of the surgical procedure was similar in both groups. The baseline comparisons between the two groups will be done using chi-squared test for categorical variables and independent two sample t-test for all continuous variables. Statistical significance will be defined at the  $p < 0.05$  level. We will use Kaplan-Meier curves and proportional hazard regression models to account for time-to event and censoring of the data.

In addition, exploratory subgroup analyses will be performed on the main endpoint including variables such as tumour size, grade and axillary nodal involvement. These will be stipulated in the Statistical Analysis Plan agreed by the International Steering Committee before any analysis is undertaken.

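### The five-year non-inferiority test leaves the handling of loss to follow-up unstated and has no censoring-aware or policy-adherent check against the 2.5-point margin

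*Combined protocol and SAP*

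**What the plan says.** SAP 8.2 sets the basis of comparison: "The two arms of the trial will be compared on the basis of 'intention to treat". Item 1 then reads: "Non-inferiority will be tested using the difference in binomial proportions of local recurrence in the first 5 years and its 90% confidence interval", using methods described only as standard. Item 2 brings in log-rank and Wilcoxon tests, Kaplan-Meier curves and proportional hazards models to deal with censoring, and then adds: "however, these shall not be used for testing non-inferiority".

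The SAP does not say who is in the denominator or how a woman last seen recurrence-free before five years is counted. The nearest guidance is protocol 9.4, where intention to treat means that "all randomised patients will be analysed".

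Other parts of the plan bear on the point:

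- SAP 8.2 reports five-year Kaplan-Meier estimates with 95% intervals for each arm.
- SAP 3 and 10 set a five-year completeness target of 95%. Of the earlier figure, section 10 says "this was 93.5% at the time of the last publication".
- SAP 10 plans checks, with modelling, for follow-up bias by arm and centre.
- SAP 10 also plans analyses by treatment received, with its own caution: "however, the results of these artificially created groups need to be interpreted" in the light of the risk-adapted approach.

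None of these compares a censoring-aware or policy-adherent difference with the margin.

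**The concern.** In a non-inferiority comparison, anything that makes the arms look alike works against the null hypothesis that the test is meant to protect. Two such influences are possible here.

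The first is loss. If a woman lost at year two stays in the denominator as recurrence-free, her unobserved three years count as event-free time. Both crude rates fall and, with equal loss, so does their difference. The plan names methods that handle this and then excludes them from the one test where it matters.

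The second is departure from the assigned policy. A woman allocated IORT who receives EBRT instead, for reasons outside the centre's declared policy, carries something close to the EBRT risk into the IORT arm. The treatment-received groups cannot check for this: the risk-adapted rule sends women with adverse pathology to both treatments, so the groups differ in prognosis.

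At stake is whether a non-inferiority conclusion near the margin can be trusted at its nominal 5% error.

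**Working it through.** **1. The plan's own figure.** Protocol 9.1 says "This is a Non-Inferiority Trial – One Sided design", with a 6% control rate, a 2.5-point margin, 80% power and 1116 per arm. With one-sided 5%:

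n = (1.645 + 0.842)² × 2 × 0.06 × 0.94 / 0.025² = 1115.8, so 1116.

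This reproduces exactly. One-sided 2.5% would need 1417, so the design level matches the SAP's 90% interval. No allowance for loss is stated.

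**2. Inputs for the check.**

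- True rates at the margin: 6% (EBRT) and 8.5% (IORT), from protocol 9.1.
- Size: 3451 randomised (SAP 10), taken as 1725 per arm. This pools the strata, whose sizes are not given.
- Assumed: constant recurrence hazard, loss spread evenly over five years, no deaths, lost women kept in the denominator as recurrence-free. Loss fractions L are illustrative unless noted.

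**3. Formulas.** The chance that a lost woman's recurrence is seen before she is lost is

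e(p) = 1 − p / [−ln(1 − p)], giving e(0.06) = 0.0303 and e(0.085) = 0.0431.

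Crude rate = (1 − L)p + L·e(p).

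False non-inferiority = Φ[(0.025 − d)/se − 1.645], where d is the crude difference and se² = [p₁(1 − p₁) + p₂(1 − p₂)]/1725, using the crude rates.

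**4. Worked case, 5% loss in each arm.**

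- EBRT: 0.95 × 0.06 + 0.05 × 0.0303 = 0.0585
- IORT: 0.95 × 0.085 + 0.05 × 0.0431 = 0.0829
- d = 0.0244 and se = 0.00872, so Φ(0.07 − 1.645) = 5.8%

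**5. Other loss patterns.**

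| Loss EBRT / IORT | Difference (points) | False non-inferiority |
|---|---|---|
| none | 2.50 | 5.0% |
| 5% / 5% | 2.44 | 5.8% |
| 6.5% / 6.5% (the earlier 93.5%) | 2.42 | 6.0% |
| 10% / 10% | 2.38 | 6.6% |
| 20% / 20% | 2.26 | 8.8% |
| 5% / 10% | 2.23 | 9.1% |
| 10% / 5% | 2.59 | 4.0% |

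If everyone lost were lost at entry, 5% equal loss would give 2.38 points and 6.7%. With 1116 per arm, the 5% / 5% and 5% / 10% cases give 5.6% and 8.2%. At an assumed 1% control rate (1% against 3.5%, 1725 per arm), 5% equal loss gives 6.4%.

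**6. Direction.** In points, with L as fractions, d = 2.50 − 4.19 × L(IORT) + 2.97 × L(EBRT). Loss therefore enlarges the difference once EBRT loss exceeds 4.19/2.97 = 1.41 times IORT loss. The last row of the table is such a case. The threshold depends on the rates: at 3.0% against 5.5%, loss of 12% EBRT and 6% IORT gives 2.52 points.

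**7. A censoring-aware difference.** In 20,000 simulated trials with 1725 per arm, the five-year Kaplan-Meier difference with a 90% interval stayed at about 2.51 points, with 4.8% to 5.0% error at every equal-loss level tried.

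**8. Out-of-policy crossover.** The documents give no rate. If a fraction c of the IORT arm takes the EBRT risk, d = 2.5 × (1 − c). For c of 5%, 10% and 15% this is 2.38, 2.25 and 2.13 points, with 6.6%, 8.7% and 11.2% error. Combining 5% equal loss with 10% crossover gives 2.20 points and 9.8%.

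**The case against.** The strongest reply has four parts.

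- **The premise is inferred.** The SAP never says that lost women count as recurrence-free. With a denominator restricted to known five-year status, uninformative loss would not dilute the difference in this way. This stands, and it is why the conclusion is conditional. But an unstated denominator in the test of the main hypothesis is itself a gap.
- **The completeness target limits the effect.** At 5% loss the shift is 0.06 points. This stands for loss alone, and the 5% / 10% case lies outside the target. The limit is not firm, however. The section 10 definition counts women who withdrew consent, or who were seen recently but short of five years, as complete, and the threshold may be reconsidered with the Trial Steering Committee.
- **Other safeguards exist.** Per-arm Kaplan-Meier estimates, bias checks, treatment-received analyses and repeats in the earlier cohorts are planned, and the SAP deliberately plays down non-inferiority. All true, but none yields a censoring-aware or policy-adherent difference judged against 2.5 points.
- **The declared test should not be replaced.** This is a third unblinded analysis, the design was sized on binomial proportions, and SAP 8.1 objects to estimates that censor at death. This stands. It argues for a supporting analysis, with death as a competing event. Without loss, that estimate equals the all-randomised binomial proportion.

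**Conclusion.** The gap is real and modest in size. The non-inferiority test is binomial and by intention to treat, its denominator and handling of loss are unstated, and nothing that handles censoring or policy adherence is compared with the margin. On the likely reading, 5% equal loss moves 2.50 points to 2.44 and false non-inferiority from 5.0% to 5.8%. An illustrative 5% EBRT / 10% IORT loss gives 2.23 points and 9.1%. These figures rest on the 6% design rate, 1725 per arm pooled over strata, even loss over time and lost women counted as recurrence-free.

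A reader might infer three stronger things that the documents do not support:

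- That loss always pulls toward non-inferiority. It does not: sufficiently heavier EBRT-arm loss reverses the direction.
- That the 10 to 15% of IORT patients expected to receive added EBRT (protocol section 2) are non-adherent. They are following the strategy under test.
- That the whole plan is confined to intention to treat without time-to-event methods. That is true only of the non-inferiority test.

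**What to change.** Keep the binomial test and make these changes to SAP 8.2:

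1. In item 1, state the denominator and how women lost or withdrawn before five years without recurrence are counted.
2. Pre-specify, as a supporting analysis, the difference in five-year cumulative incidence of local recurrence, with death as a competing event and loss and withdrawal censored. Give its confidence interval at the same level as the binomial one and compare it with 2.5 points.
3. Narrow the exclusion in item 2 so that it does not bar this analysis.
4. Repeat the comparison, as randomised, as a sensitivity analysis in a policy-adherent set. Count EBRT added under the centre's declared policy as adherent.
5. Report any disagreement with the binomial result.

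No new data should be needed. The cost is SAP wording and a little more analysis work, and the added interval may be less favourable than the binomial one.

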**Local recurrence in the conserved breast:** Histologically or cytologically proven recurrence of tumour in the index breast. (censored=last date known to be alive, withdrawn, or dead)

**Index quadrant recurrence:** Local recurrence as in 1 above in the index quadrant. (censored=last date known to be alive, withdrawn, dead, other quadrant recurrence)

**Scar recurrence:** Local recurrence as in 1 above within 1cm of the scar. (censored=last date known to be alive, withdrawn, dead, non-scar recurrence)

**Other quadrant recurrence:** Local recurrence as in 1 above in other quadrants. (censored=last date known to be alive, withdrawn, dead, index quadrant recurrences)

**Invasive local recurrence in the conserved breast:** As in 1 above, excluding those with only in-situ disease. (censored=last date known to be alive, dead, withdrawn)

**Survival without invasive local recurrence:** As in 2 above, excluding those with in-situ disease (censored=last date known to be alive, withdrawn, any other type of relapse)

**Isolated local recurrence in the conserved breast:** As in 1 above, excluding those with distant disease within 3 months of local recurrence. (censored=last date known to be alive, dead, withdrawn)

**Survival without isolated local recurrence:** As in 2 above, excluding those with distant disease within 3 months of local recurrence. (censored=last date known to be alive, withdrawn, any other type of relapse)

**Overall survival:** The time interval between randomisation and death. (censored=last date known to be alive or withdrawn)

**Breast cancer survival:** The time interval between randomisation and breast cancer death (censored=last date known to be alive or withdrawn)

**Non-Breast-cancer survival:** The time interval between randomisation and non-breast-cancer death (also, cardiac and other cancer deaths separately) (censored=last date known to be alive or withdrawn)

Lung cancer and heart disease deaths (if possible as a subset analysis in smokers) and effect of laterality on non-breast cancer deaths [appendix], and correlation with EBRT dose.

**Disease free survival:** The time interval between randomisation and any type of breast cancer relapse or any death (censored=last date known to be alive, withdrawn)

Toxicity of surgery and radiotherapy as previously described.

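### SAP 8.2 plans a single hazard ratio for local recurrence with no split at 5 years, although SAP 8.1 expects the difference to stop growing then

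*Combined protocol and SAP*

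**What the plan says.** SAP 8.1 argues from earlier randomised trials of radiotherapy against no radiotherapy that the effect on local recurrence "plateaus at 5 years and no additional difference arises between 5 and 20 years". It carries this over to the present comparison, concluding that "the absolute difference in local recurrence is highly unlikely to change after the first 5 years".

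SAP 8.2 item 1 tests non-inferiority on the difference in 5-year proportions of local recurrence, with a 90% confidence interval. Item 2 adds the tests of difference: "We shall also test for any difference in survival function using the log-rank test and Wilcoxon tests, and Kaplan-Meier curves and proportional hazard regression models". It goes on to say that "these shall not be used for testing non-inferiority". Items 3 and 4 add the integrated difference between the curves and restricted mean survival time (RMST). The main description is event counts and 5-year Kaplan-Meier estimates by arm.

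Item 2 gives no horizon, no period-specific hazard ratio and no check of proportional hazards. SAP section 10 defines the censoring of local recurrence only as "censored=last date known to be alive, withdrawn, or dead". The same section notes that the "protocol specifies at least 10 year follow up of every patient", and it expects a median of 10 years in the first 1222 women. Protocol 9.4 says of local recurrence that "the logrank test will be used", also with no horizon.

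**The concern.** A gap between the arms that opens by year 5 and then stays constant means roughly equal hazards afterwards. That is non-proportional hazards, and it is the SAP's own expectation. A proportional-hazards model fitted to all follow-up then averages an early ratio with later ratios near 1, and the average moves closer to 1 as follow-up lengthens. The log-rank test gains variance without gaining signal.

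Two things are at stake. First, the hazard ratio that readers see would understate whatever early difference exists, in either direction. Second, the SAP relies on the plateau to present the 5-year difference as close to final. Its evidence compares radiotherapy with none, not intraoperative (IORT) with external beam radiotherapy. One overall ratio cannot show whether the plateau holds in this trial.

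**Working it through.** **1. The plan's own figure.** Protocol 9.1 starts thus: "With a baseline relapse rate of 6 % at 5 years". The margin is 2.5 points and the power 80%; one-sided 0.05 is implied by the 90% interval.

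n per arm = (1.645 + 0.842)² × 2 × 0.06 × 0.94 / 0.025² = 6.183 × 0.1128 / 0.000625 = 1115.8, that is 1116, as stated.

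This is a non-inferiority size. The documents state no power for the log-rank test, so the rest is illustration.

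**2. Does a constant difference imply a ratio near 1?** With 6% v 8.5% at 5 years, equal event rates afterwards give a hazard ratio of 0.94 / 0.915 = 1.03 just after year 5. Equal hazards is therefore a fair model of the plateau.

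**3. Inputs.**
- From the documents: 6% and 8.5% at 5 years (Protocol 9.1); 3451 women (SAP section 10).
- Assumed: constant hazards within 0-5 years, the control hazard in both arms afterwards, 1.5% deaths per year as censoring, equal arms, and the same follow-up for every woman.

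Hazards: control −ln(0.94)/5 = 0.01238 per year; IORT −ln(0.915)/5 = 0.01777 per year.

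**4. Formulae.** Let d0 and d1 be the expected events in a short interval (control, IORT) and π the IORT share of women at risk.
- U = Σ[d1 − (d0 + d1)π]
- V = Σ(d0 + d1)π(1 − π)
- average hazard ratio ≈ exp(U/V)
- z = U/√V; power at two-sided 0.05 = Φ(z − 1.960)

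With equal hazards after year 5, each later term of U is zero while V keeps growing.

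| Follow-up (years) | Events | U | V | Hazard ratio | z | Power |
|---|---|---|---|---|---|---|
| 5 | 241.2 | 21.59 | 60.29 | 1.43 | 2.78 | 79% |
| 7 | 312.7 | 21.59 | 78.17 | 1.32 | 2.44 | 69% |
| 8 | 347.0 | 21.59 | 86.75 | 1.28 | 2.32 | 64% |
| 10 | 412.9 | 21.59 | 103.22 | 1.23 | 2.13 | 57% |
| 12 | 475.3 | 21.59 | 118.81 | 1.20 | 1.98 | 51% |

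At 10 years the share of the log hazard ratio that remains is 60.29 / 103.22 = 58%.

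**5. Sensitivity at 10 years: power cut at 5 years, then over all follow-up.**
- 6% v 8.5%, 3451 women, p<0.001 (the SAP's level for local recurrence): 30.5% and 12.2%, a loss of 18 points.
- 6% v 8.5%, 2232 women, p<0.001: 14.6% and 5.7%, a loss of about 9 points.
- Assumed 1% v 3.5%, 3451 women, 0.05: 99.8% and 98.4%, a loss of 1.4 points. The ratio still falls, from 3.08 to 2.23.
- 6% v 8.5%, 3451 women, 0.05, later hazard half the control hazard: 79% and 66%, a loss of 13 points.
- Proportional hazards throughout, 6% v 8.5%, 3451 women, 0.05: 79% and 97%, so the 5-year cut is the weaker test.

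**6. Precision of an after-5-year ratio.** With 10 years of follow-up and 6% v 8.5%, events after year 5 number 412.9 − 241.2 = 171.7. The standard error of the log ratio is about 2/√171.7 = 0.153, and exp(1.96 × 0.153) = 1.35. A true ratio of 1 would carry an interval of about 0.74 to 1.35. With 1% v 3.5% there are 105.0 − 74.8 = 30.2 later events, a standard error of 0.364, and an interval of about 0.49 to 2.04.

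**The case against.** The strongest reply is that nothing decisive rests on item 2. The SAP excludes these methods from the non-inferiority test, fixes that test and the main estimates at 5 years, and prefers absolute numbers to relative risks. It also plans methods that do not need proportional hazards: RMST and the integrated difference, with the Wilcoxon test giving more weight to early events. All of this stands, and it limits the point to a supporting analysis. It does not remove it. None of these methods corrects a hazard ratio that is reported. The SAP's stated reason for RMST is normality (though papers it cites concern doubtful proportional hazards), and it gives no RMST horizon. In simulation with 2232 women, 6% v 8.5% and 10 years of follow-up, Wilcoxon power was 44%, between 40% for the full log-rank and 61% for a 0-5 year log-rank.

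A second reply is that the plateau is offered as a reason for reporting at 5 years, not as a hazard model. That is fair, and it is why the overall ratio should stay. It is also a reason to check the plateau.

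A reader might infer more than the documents support:
- That the non-inferiority conclusion is diluted. It is not, because later events do not enter it.
- That the dilution favours IORT. That holds only if IORT does worse early; if it does better, the same dilution hides a benefit.
- That a loss of about 20 points of power is a property of the plan. The documents give neither the follow-up distribution nor the later hazards, and the loss varies widely with the assumptions. The 6% rate may itself be too high, since Protocol 9.2 reports an overall 0.3% at two years.
- That a 0-5 year log-rank should replace the planned one. Under proportional hazards it would give up power (79% v 97%), and the change would come after two unblinded analyses.

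**Conclusion.** The inconsistency is real and lies within the SAP: section 8.1 implies a hazard ratio near 1 after year 5, while section 8.2 summarises with a proportional-hazards model and no time split. That the model covers all follow-up is inferred from the censoring rule and the absence of a horizon; the SAP does not say so outright.

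If the plateau holds, the overall ratio is diluted. Under the protocol's 6% v 8.5% with 3451 women and the assumptions listed, 1.43 becomes 1.32 at 7 years and 1.20 at 12, and log-rank power at 0.05 falls by 10 to 28 points over that range. Other assumptions give losses as small as 1.4 points. The main conclusion is unaffected. The lasting gap is that the plan has no analysis designed to test the plateau it relies on. Severity: CONSIDER.

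**What to change.** In SAP 8.2 item 2, for local recurrence:
- fit the Cox model with follow-up split at 5 years, and report the hazard ratio with its 95% confidence interval for 0-5 years and for after 5 years, beside the overall ratio;
- name the after-5-year ratio as the check of the plateau in 8.1;
- keep the full-follow-up log-rank as the planned test, and show a log-rank limited to 0-5 years as a supporting result only.

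The cost is a few words of SAP text and one further model, with no new data. The drawback is that the after-5-year ratio is less precise, and markedly so if recurrence is rare. A wide interval around 1 should be read as a weak check, not as proof of a plateau.
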